### Variables

The primary outcomes will be sexual function and fertility-related distress. Secondary outcomes will be body image, anxiety and depression, health-related quality of life, self-efficacy related to sexuality and fertility, and fertility-related knowledge. Primary and secondary variables will be collected in the survey. Before conducting the Fex-Can Cohort, the primary outcomes were tested in two pilot studies: one including young women diagnosed with breast cancer (*n* = 181) [7], and one including young men diagnosed with testicular cancer (*n* = 111) [11]. The results showed the instruments to be well accepted. All primary and secondary outcomes will be included in the survey at each assessment. Additionally, background variables (see below) will be collected via the survey at baseline and at follow-ups. Clinical variables (diagnosis, stage, treatment, relapse) will be extracted from registry data and updated in connection with each data collection. See Table 1 for overview of assessments.

**Table 1 Tab1:** Overview and timing of assessments in the Fex-Can Cohort

Type of data	Time of diagnosis / treatment start	Baseline 1.5 years	Follow-up 3 years	Follow-up 5 years
Mode of administration				
Survey data				
Background variables		X	X	X
Sexual function (SexFS v2)		X	X	X
Fertility-related distress (RCAC)		X	X	X
Anxiety and depression (HADS)		X	X	X
Health-related quality of life (EORTC QLQ-C30)		X	X	X
Body Image (BIS)		X	X	X
Self-efficacy		X	X	X
Fertility-related knowledge		X	X	X
Clinical data	X^a^	X^b^	X^b^	X^b^

^a^Extraction of data from respective quality registry at time of baseline-assessment

^b^Updated information extracted from the quality registries in connection to analyses

#### Cancer group – survey

##### Background variables

Background variables collected in the survey will include sociodemographic information on country of birth, educational level, occupation, partner relationship, children, and sexual orientation. Information on current cancer treatment and the use of fertility preservation procedures will also be included.

##### Sexual function

The Patient-Reported Outcomes Measurement Information System© Sexual Function and Satisfaction Measure version 2 (SexFS v2) is a measure assessing sexual function and satisfaction in men and women regardless of sexual orientation [26]. Items in the SexFS v2 are scored on a five-point scale (ranging from 1 = None/Not at all to 5 = Very/A lot). In this study four specific domains for women will be included: Vaginal lubrication, Vaginal discomfort, Vulvar discomfort – clitoral, and Vulvar discomfort – labial. For males, the specific domain Erectile function till be used. Additionally, four gender-neutral domains will be included for all participants: Interest in sexual activity, Orgasm – ability, Orgasm – pleasure, and Satisfaction with sex life. Item response theory is used to calculate domain scores, which are transformed to a T-score metric where 50 represents the mean for sexually active American adults (standard deviation = 10) [26]. The SexFS v2 has shown adequate content, construct and known-groups validity as well as test-retest reliability [26, 27]. The selected items and domains of the SexFS v2 were translated into Swedish and linguistically validated in accordance with the procedure developed by FACITrans and PROMIS [28].

##### Fertility-related distress

Fertility-related distress will be assessed using the Reproductive Concerns After Cancer (RCAC) scale. The RCAC is a multidimensional measure, assessing a range of concerns related to fertility and parenthood, developed and evaluated for young adult female cancer survivors [29] and recently adapted for male cancer survivors [30]. The scale includes 18 items in six dimensions (3 items each) scored on a five-point scale (ranging from 1 = Strongly disagree to 5 = Strongly agree). The following dimensions are included in the RCAC: Fertility potential, Partner disclosure, Child’s health, Personal health, Acceptance, and Becoming pregnant/Achieving pregnancy. In each dimension, a high level of reproductive concerns reflects fertility-related distress and is defined as a mean score > 4. The RCAC has demonstrated satisfactory internal consistency and construct validity [19, 30, 31]. The original scale for females was translated into Swedish by two bilingual researchers. In parallel to this, a Swedish version for males was developed in collaboration with [name], creator of the original RCAC. Subsequently, these versions were evaluated by one bilingual panel (*n* = 4), one lay panel (*n* = 7) and one patient panel (*n* = 8), as well as by cognitive interviews with 3 young persons with a cancer experience. The Swedish versions have been used in women with breast cancer [7] and men with testicular cancer [11] and shown to be well accepted. Internal consistency in the female version was shown to be good with exception for ‘Becoming Pregnant’ with a Cronbach’s α coefficient of 0.54 [7]. In the male version, internal consistency was acceptable (Cronbach’s α coefficients: 0.64–0.90) in all dimensions [10].

##### Body image

Body image will be assessed with the Body Image Scale (BIS) that measures perception of one’s body image associated with cancer and cancer treatment [32]. The BIS comprises 10 items and responses are given on a four-point scale (ranging from 0 = Not at all to 3 = Very much) with higher scores indicating a more negative body image. Total summary scores can range between 0 and 30, and a total score exceeding 10 is suggested to reflect a negative body image reaching a clinical level [32, 33]. The BIS has shown high test-retest reliability and satisfactory internal consistency in cancer patients [32].

##### Anxiety and depression

The Hospital Anxiety and Depression scale (HADS) measures anxiety and depression in two subscales [34]. Each subscale consists of 7 items and responses are given on a four-point scale (ranging between 0 and 3) with higher scores indicating more distress. Subscale scores can range between 0 and 21, with scores above 7 indicating borderline or clinically significant cases of anxiety or depression, respectively. The subscales have been reported to have satisfactory internal consistency and the concurrent validity has been reported to be good to very good [35].

##### Health-related quality of life

The EORTC QLQ-C30 (version 3.0) will be used to measure health-related quality of life [36, 37]. The instrument includes five functional scales, three symptom scales, a global health status scale, and six single items. All scores will be linearly transformed to a score between 0 and 100. For the functional and the global QoL scales, higher scores indicate better health. For the symptom scales, higher scores indicate more symptom burden. The scale has demonstrated good psychometric properties in cancer populations [36, 38].

##### Self-efficacy

Self-efficacy related to sexuality and fertility will be assessed by study-specific questions measuring confidence in one’s own ability to handle situations, thoughts and emotions related to sexuality (6 items) and to the threat of infertility (6 items). Examples of statements assessing self-efficacy are “I feel confident that I can handle negative thoughts and emotions in relation to my sex life” and “I feel confident that I can cope with meeting friends or relatives who are pregnant”. The items are scored on a four-point scale (ranging from 1 = Strongly disagree to 4 = Strongly agree) and an additional response alternative “Not relevant”. Total mean scores will be calculated, with higher scores indicating higher levels of self-efficacy related to sexuality and fertility, respectively.

##### Fertility-related knowledge

Perceived level of knowledge about general and cancer-related fertility issues will be examined by a study-specific questionnaire with 10 items rated on a four-point scale (ranging from 1 = Disagree completely to 4 = Agree completely). Examples of items are: “I have good knowledge regarding the chance of becoming pregnant at one attempt” and “I have good knowledge regarding the effect of cancer and cancer treatments on reproductive ability”. Total mean scores will be calculated, with higher scores indicating higher levels of perceived fertility-related knowledge.

#### Cancer group - registry data

After receiving formal consent from each registry, the following clinical data will be collected from the Swedish National Quality Registries for Brain Tumors, Breast Cancer, Gynecological Oncology, Lymphoma, and Testicular Cancer: date of diagnosis, clinical stage, type of treatment, relapse, adverse events, secondary cancers and performed fertility preservation. The clinical variables were selected in close collaboration with representatives from each National Quality Registry.

#### Comparison group - survey

The survey administered to the comparison group will include the same instruments as for the cancer group with the exception of the study-specific measures of fertility-related knowledge and self-efficacy related to fertility. Furthermore, specific items related to having had cancer will be deleted from the BIS (5 items) and the RCAC (9 items constituting 3 dimensions: Partner disclosure, Child’s Health, Personal Health). The shortened versions of the BIS and RCAC have not been validated. However, the shortened BIS has been used in a previous study on sexual functioning in the general Dutch population showing a Cronbach’s α coefficient of 0.86 [39].

#### Administration of instruments

Study-specific items and instruments to the cancer group will be administered in the same order at all assessments: BIS; RCAC; Self-efficacy Fertility; Fertility-related knowledge; Self-efficacy Sexuality; SexFS v2; HADS; and EORTC QLQ-30. The comparison group will only be assessed once with study-specific items and instruments, given in the same order as for the cancer group.

### Sample size

Based on official statistics on cancer incidence in Sweden [2, 40] the eligible population is estimated to approximately 1500 for the inclusion period. Based on our experience of moderate response rates (50–60%) in surveys on sensitive issues in this age group when no incentives were offered [7, 11], we expect the addition of incentives (2 cinema tickets) to result in a larger proportion of responders. An estimated response rate of 70% would result in 1050 participants at baseline. At baseline, a majority of participants (≈80%, *n* = 840) are expected to rate sexual dysfunction or fertility-distress meeting the inclusion criteria for the embedded RCT [23]. Of those invited to the RCT, about half are expected to consent participation (*N* = 420) and these will be excluded for further follow-up in the Fex-Can Cohort, leaving 630 participants for the longitudinal analyses. Attrition in the Fex-Can Cohort due to deaths and other reasons for non-response is estimated to 15% at following assessments, giving an estimated response rate at T2 (*n* = 535) and T3 (*n* = 454). Sample size determination was based on the recommendation to include at least 5 events of the dependent variable of interest (in this case: the primary outcome measures SexFS and RCAC) for each independent variable included in the multivariable logistic regression models [41]. Thus, we estimated that at least 50 events of the dependent variable in the sample are required in order to include up to ten independent variables. Based on the incidence rates of the selected diagnoses, we expected a distribution of approximately 65% women and 35% men in the eligible sample. Previous data of sexual dysfunction and fertility distress in the Swedish setting [7, 11] indicate that the number of events of the dependent variables at baseline is ≈30% for males and ≈60% for females. Based on these numbers, we estimate the sample size to be sufficient for determination of potential predictors for both sexes at all assessment occasions, including the 5-year follow-up. As the Fex-Can Cohort is an observational study, no formal power calculation was conducted.

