### Statistical methods

The study will be reported following the STROBE statement [42] and the SPIRIT-PRO Extension [43]. Descriptive statistics will be used to determine the prevalence of sexual dysfunction and fertility-related distress by diagnosis and sex. These will be presented as means and standard deviations and as percentages of participants above the described cut-offs for these outcomes. Prevalence rates in the cancer group will be compared to prevalence rates in the general population by sex and age group, using Students’ t-test and χ^2^ tests. To determine predictors for sexual dysfunction and fertility-related distress at each assessment we will perform logistic regression models for each primary outcome (SexFS v2-domains and RCAC-dimensions) for the whole group and by sex. Independent variables will include sex (whole group), partner status, parenthood status, child wish (only for RCAC), satisfaction with sex life pre-diagnosis (only for SexFS v2), diagnosis, treatment intensity, body image, anxiety, and depression. Trajectories of these issues over time (T1, T2 and T3) will be analyzed with linear mixed models. Relations between sexual dysfunction and fertility-related distress, and between these issues and our secondary outcomes, will be analyzed with Pearson’s correlation coefficients. Statistical analyses will be performed in collaboration with external statisticians.

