## Discussion

This population-based cohort study aims to determine the prevalence and predictors of sexual dysfunction and fertility-related distress in young adults diagnosed with cancer. The results of the study will increase understanding of the trajectories of sexual dysfunction and fertility-related distress over 5 years following diagnosis.

Our study design includes a large nationwide sample of young adults diagnosed with different cancers and will therefore establish prevalence rates of sexual dysfunction and fertility-related distress over the first 5 years after diagnosis. One of the selected diagnoses, brain tumors, is a cancer often excluded in this kind of research and the group’s sexual dysfunction and fertility-related distress is still largely unknown. Potential participants will be identified through National Quality Registers with excellent coverage, ensuring that all individuals in the age group diagnosed with the selected cancers will be approached [44]. The design also allows for analyses of non-responders and attrition including highly reliable clinical variables. At the baseline assessment some patients may still be on treatment (e.g. lymphoma and breast cancers) and others will have finished their treatment (e.g. testicular cancer). Therefore, treatment status will be described in detail for each diagnosis when reporting prevalence at baseline, and all models will control for current treatment status. While most of the selected patient-reported outcome measures are standardized instruments, it should be noted that the study-specific measures, as well as the shortened versions of the BIS and RCAC for the comparison group, have not been validated. With a young adult comparison group assessed with the same standardized measures it will be possible to determine to what extent the self-rated problems are related to being treated for cancer. As the prevalence of sexual dysfunction in women and men has been reported to vary between countries [45, 46], the use of a comparison group randomized from the total general population in the country is a strength. However, the fact that the comparison group is only assessed at one time point is a limitation as it does not allow comparison of trajectories of these issues over time.

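### Only RCT-eligible participants can leave the cohort for the embedded RCT, so 3- and 5-year prevalence from the remaining 630 is understated unless the analysis corrects for it

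*Protocol article*

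**What the plan says.** The Sample size section gives the participant flow. It starts from about 1500 eligible people, and "An estimated response rate of 70% would result in 1050 participants at baseline". About 80% of these (840) "are expected to rate sexual dysfunction or fertility-distress meeting the inclusion criteria for the embedded RCT". On uptake, "Of those invited to the RCT, about half are expected to consent participation", which gives 420. Of the 420 it says that "these will be excluded for further follow-up in the Fex-Can Cohort, leaving 630 participants for the longitudinal analyses". Later loss "due to deaths and other reasons for non-response is estimated to 15% at following assessments", giving 535 at T2 and 454 at T3.

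The Statistical methods section plans logistic models for each SexFS domain and each RCAC dimension at every assessment. It adds: "Trajectories of these issues over time (T1, T2 and T3) will be analyzed with linear mixed models". It does not mention RCT enrolment.

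The Discussion says that the nationwide sample "will therefore establish prevalence rates of sexual dysfunction and fertility-related distress over the first 5 years after diagnosis". It mentions non-responder and attrition analyses using registry data and concedes in general terms that attrition may cause bias. It does not name removal into the RCT as a source of bias or as a limitation.

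**The concern.** Removal into the RCT is planned, takes 40% of the cohort (420/1050), and depends on the outcome. A participant must report sexual dysfunction or fertility distress at baseline to be eligible, so the 210 who do not meet the criteria all stay and half of the 840 who do are expected to go. The people followed to 3 and 5 years are therefore less affected at the start than the cohort they came from.

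Three stated outputs rest on that remainder: prevalence after baseline, the T1–T3 trajectories, and the predictor models at T2 and T3. Reported without correction or caveat, the later prevalence would describe a selectively less affected group as if it were the national population of young adults with these cancers.

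**Working it through.** **1. Reproduce the plan's flow.** All inputs are from the Sample size section.
- Baseline: 1500 × 0.70 = 1050
- RCT-eligible: 1050 × 0.80 = 840; not eligible: 210
- Enter the RCT: 840 × 0.50 = 420
- Remain: 1050 − 420 = 630, made up of 420 eligible and 210 not eligible
- T2: 630 × 0.85 = 535.5 (stated 535); T3: 535.5 × 0.85 = 455.2 (stated 454)

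The flow reproduces within rounding.

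**2. Eligible share before and after removal.** Before: 840/1050 = 80%. After: 420/630 = 66.7%, which is 13.3 points lower. With RCT consent c, the retained share is 0.8(1 − c)/(1 − 0.8c). If c is varied from 30% to 70% (an assumed range), the share runs from 73.7% to 54.5%.

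**3. A single outcome.** The 80% is a composite, whereas the analyses are per domain or dimension. The plan gives event rates of about 30% in men and 60% in women. Suppose that 80% of each sex is eligible, that every event lies among the eligible, and that half of the eligible leave. Retained baseline prevalence is then p × 0.5/(1 − 0.4):
- Men: 0.30 × 0.5/0.6 = 25%
- Women: 0.60 × 0.5/0.6 = 50%

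These gaps of 5 and 10 points are the largest under that uptake. They shrink if some events lie outside the eligible group.

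**4. Carry-over to follow-up (composite).** Let q be the probability that an affected person is affected later, and r the probability that an unaffected person becomes affected. Both are assumed. Full-cohort prevalence is 0.8q + 0.2r; in the retained group it is 0.667q + 0.333r. The gap is 0.133(q − r).

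| q, r | Full cohort | Retained | Gap (points) | Change from T1, full | Change from T1, retained |
|---|---|---|---|---|---|
| 1, 0 | 80.0% | 66.7% | 13.3 | 0 | 0 |
| 0.9, 0.1 | 74.0% | 63.3% | 10.7 | −6.0 | −3.3 |
| 0.8, 0.2 | 68.0% | 60.0% | 8.0 | −12.0 | −6.7 |
| 0.5, 0.5 | 50.0% | 50.0% | 0 | −30.0 | −16.7 |

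In the middle rows the retained group understates a real improvement. If T1 is instead reported on 1050 and T2 on the retained group only, prevalence appears to fall by 13.3 points when nothing has changed (first row).

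**5. Simulation on continuous scores, no true change.** Scores are normal, 80% are eligible at T1, and half of the eligible are removed at random.
- Eligibility on the one analysed score, retest correlation 0.5 to 0.7: T2 prevalence is about 76% to 74% against a true 80%. The retained group starts 0.23 SD too healthy and shows a false worsening of 0.12 to 0.07 SD.
- Eligibility on any of 5 to 14 domains, inter-domain correlation 0.2 to 0.5, retest 0.6: per-domain T2 prevalence is understated by roughly 2 to 4 points (1.4 at the lowest setting, 4.0 at the highest). Allowing retest 0.5 to 0.7, the false change is about 0.03 to 0.08 SD, or 0.3 to 0.8 T-score points on the SexFS metric (SD 10).

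**6. Effect of weighting.** Give retained eligible participants weight 1/(1 − 0.5) = 2 and the others weight 1: 840/(840 + 210) = 80%. The Kish effective size is (420 × 2 + 210)²/(420 × 4 + 210) = 1,102,500/1890 = 583. This is 92.6% of 630, a loss of about 7%.

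**The case against.** There is a good reason to stop cohort follow-up of RCT participants: the intervention may alter their later scores. That stands, and nothing here asks for those scores to be used as natural history. It does not justify setting aside their T1 data or leaving the remainder unweighted.

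The phrase about follow-up ends later surveys; it does not delete T1 records. The methods sentence on mixed models is compatible with using every available record, including baseline-only ones. In the single-score simulation a mixed model that keeps all T1 scores shows no false change. This objection has force. The trajectory problem is conditional on the 630 being the modelled set, which is what the Sample size wording says but the methods sentence does not repeat.

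Weighting and missing-data methods are commonly left to a full protocol or SAP, which is not shown. That also stands, so silence on weights is not the defect. The point rests on what the article does state: an outcome-dependent exclusion, a named longitudinal sample of 630, and an unqualified five-year prevalence claim.

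A reader might infer that follow-up prevalence is simply 13 points too low. The documents do not support that: 13 points applies to the composite under full persistence, and the plan analyses domains and dimensions separately. A reader might also infer that the mixed models will show a spurious worsening. The direction is not settled: step 4 gives an attenuated improvement or an apparent fall, and step 5 a small worsening, depending on the true change and on which T1 records enter.

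**Conclusion.** The point holds as a should-fix. Following the plan as written gives 3- and 5-year prevalence that is too low for the source population, unless later status is unrelated to baseline status. The fall in the eligible share from 80% to 66.7% follows directly from the plan's figures. The resulting bias at follow-up rests on assumptions: roughly 2 to 4 points per domain under the assumed correlations, and up to 13 points for the composite.

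If only the 630 are modelled, trajectories are biased in level. Their slopes are also biased whenever change differs by baseline status, with size and direction depending on the true change. The T2 and T3 predictor models rest on the same selected sample; the effect on their coefficients has not been quantified.

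It would be wrong to conclude that the primary objective as a whole fails. Baseline prevalence, baseline predictors and the single cross-sectional comparison with the general population all precede the removal and are unaffected.

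The correction has its own assumption. RCT entry needs voluntary consent, so weighting recovers the target only if consent is ignorable given the observed baseline data. The RCT's exact criteria are not in the document.

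**What to change.** 1. State that the mixed models use all baseline records (about 1050), including the T1 data of those who enter the RCT, plus T2 and T3 data from those still followed.
2. For T2 and T3 prevalence and predictor models, weight each retained RCT-eligible participant by 1/(1 − P(enters the RCT)), with that probability modelled on T1 scores, sex, age, diagnosis and registry variables. The weight is about 2 on average; everyone else gets 1. State the assumption that consent is ignorable given these data, and report the unweighted result alongside.
3. Amend the Sample size sentence that names the 630 as the longitudinal sample. In the Discussion, qualify the five-year prevalence claim and name removal into the RCT as a limitation separate from ordinary attrition.

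Cost: analysis and wording changes only. No new data are needed, and the exclusion of RCT participants' later scores stays in place. The weights reduce the effective sample size from 630 to about 583, before the 15% attrition at each follow-up.
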